### Data collection and management

Informed consent for SPIN Cohort and external enrollees will be obtained via the *Qualtrics* survey tool. To ensure accuracy and link to SPIN Cohort data, for SPIN Cohort enrollees an email authentication check will ensure that emails entered match eligible SPIN Cohort participant emails. Data security measures in place at *Qualtrics* are described in the *Qualtrics* security statement [65].

For both the feasibility and full-scale trials, all participants will complete the outcome measures at 3 and 6 months post-randomization through *Qualtrics*. Baseline measures will be completed through regular SPIN Cohort assessments for SPIN participants and through *Qualtrics* for externally recruited participants. The SPIN Cohort uses a secure electronic data management platform designed and managed by the Information Management Services of the Centre for Clinical Epidemiology, Jewish General Hospital, Montreal. All information obtained from participants during the trial will be treated confidentially within the limits of the law. To protect the privacy of participants, a unique participant identification number has been automatically assigned to each participant (SPIN Cohort IDs for Cohort participants and SPIN-SELF IDs for external participants).

Separate from the SPIN Cohort portal, an encrypted database has been created for SPIN interventions, including the SPIN-SELF Program, which includes the usage log information of participants in the intervention group. Participant identification numbers are also available in the usage log to link participants’ intervention and regular cohort data.

During the trial, access to the cohort portal and the encrypted database will be limited to study investigators. Once the trial ends and results are reported, de-identified data will be made available upon reasonable request. No biological specimens will be collected.

### Data analysis

Consistent with the feasibility trial design and small sample size, no hypothesis tests are planned for the feasibility portion of the trial [66, 67]. Instead, we will present a description of the feasibility elements, including participants’ eligibility and recruitment and numbers and percentages of participants who respond to follow-up measures. Use of the internet intervention will be described by presenting the frequency of logins and usage of the specific SPIN-SELF modules. Analysis of outcome measures will include the completeness of data and presence of floor or ceiling effects. Descriptive statistics will be used to provide means and standard deviations for the measures. Qualitative information on participants’ experience using the SPIN-SELF intervention will be used to interpret acceptability related to the group-sessions format, content of the sessions and online program, webpage organization, and navigation. Information related to required resources and management of the program during feasibility will inform any necessary changes to intervention or trial procedures.

In the full-scale trial, we will use intent-to-treat analyses to estimate score differences between intervention and care as usual participants with a linear mixed-effects model fit using the lmer function in lme4 [68]. Score differences and Hedges’ g SMD effect size will be presented with 95% CIs. For all models, to account for clustering in the blocked PN-RCT design, we will fit a random intercept and slope for treatment effect by randomization block and an additional random slope for treatment by intervention group cluster [30, 69]. In main analyses for each outcome, in addition to a fixed effect for assignment to the intervention arm, we will include a fixed effect for baseline score. In adjusted analyses, we will also control for age (years), sex (male vs. female), SSc disease subtype (diffuse vs. limited), disease duration (years since diagnosis), and country (e.g., Canada, France, other vs. USA) as fixed effects.

To minimize the possibility of bias from missing outcome data, we will use multiple imputation by chained equations using the mice [70] package to generate 20 imputed datasets, using 15 cycles per imputed dataset. Variables in the mice procedure will include randomization block, intervention arm, number of videoconference sessions attended, measures of all primary and secondary outcomes at baseline and at 3 and 6 months post-randomization, age, sex, SSc disease subtype, years since diagnosis, country (e.g., Canada, France, UK, Australia, other vs. USA), and race/ethnicity (e.g., Black and other vs. White). Pooled standard errors and associated 95% CIs will be estimated using Rubin’s rules [71].

To estimate average intervention effects among compliers (to be defined pre-analysis based on session attendance or online program usage), we will use an instrumental variable approach to inflate intent-to-treat effects from main models by the inverse probability of compliance among intervention arm participants [72, 73]; 95% CIs will be constructed via a cluster bootstrap approach, resampling at study randomization block and participant levels [74, 75]. For transparency, results for participants with complete data will also be shown.

Participant satisfaction scores for the intervention group will be reported descriptively.

All outcome analyses will be conducted in R (R version 3.6.3; R Studio version 1.2.5042). All analyses will be 2-sided with *α* = 0.05. We will not adjust for multiple analyses since we identified a single primary outcome a priori.

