**Fig. 10 Fig10:**
[figure not shown]
Living with SSc stories page

Each videoconference-based intervention group will be led by a person with SSc who previously received training as a support group leader via our SPIN-SSLED Program [35, 36]. Group facilitators will support participants to develop self-management skills and integrate educational material from the online toolkit into their daily routines and will moderate group discussions. In addition to their previous training, prior to the trial, each peer facilitator will receive 4 additional training hours divided into 3 sessions to understand their role, including how to promote behavioral change using Specific, Measurable, Attainable, Achievable, Relevant, Time-based (SMART) goals [43–45]; incorporate strategies for communication to encourage participation and support motivation; use active listening skills; model positive feedback; and manage challenging situations.

Each of the 8 intervention sessions will last between 60 and 75 min and include 3 segments: (1) review of modules, including questions and sharing of experiences (20–25 min); (2) education on goal setting, goal achievement, and discussion of goal progress (40–45 min); and (3) presentation of new assignments (5 min). Session 1 will cover an introduction to the SPIN-SELF Program and online modules and tools. Sessions 2–4 will focus on common challenges identified as salient to most people living with SSc (fatigue, sleep, emotions, and stress) to facilitate group learning. Sessions 5 and 6 will provide participants the opportunity to select among other modules most relevant to them (e.g., coping with pain, gastrointestinal symptoms, body image concerns). Session 7 will cover the Effective Communication with Health Care Providers Module. Session 8 involves summarizing progress and planning for the future. Sessions 1 to 4 will be weekly, after which sessions 5 to 8 will be scheduled bi-weekly (8 sessions in 12 weeks in total). See Table 2.

**Table 2 Tab2:** Outline of SPIN-SELF videoconference group sessions

Session number	Week	Session topic
1	1	• Welcome • Introduction to self-management • Introduction to SPIN-SELF online modules and toolkit • *Assignment:* Review the Fatigue Module
2	2	• Introduce the SPIN-SELF Fatigue module • SMART goal setting (part 1) • Practicing setting SMART goals related to fatigue • *Assignment:* Write a goal on fatigue using the online goal form; review the Sleep Module

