### Sample size

A Cochrane Review (*N* = 7,442) of lay-led self-management programs reported a standardized mean difference (SMD) effect size of 0.3 (95% confidence interval [CI] 0.19 to 0.41) for improved self-efficacy in 10 studies [63]. With a 1:1 randomization ratio, for an assumed effect size of SMD = 0.30, two-tailed *α* = 0.05, a mean of 8 participants per group, and intra-class correlation coefficient of 0.08 (based on SPIN-CHAT results) [27], *N* = 471 provides ≥ 80% power. In our recent SPIN-CHAT [27] and SPIN-SSLED trials [35, 36], which used similar group formats, loss to follow-up was well below 10%. Assuming 10% loss to follow-up would require 524 participants. In the 3 months between March 1, 2021 and June 1, 2021, 1007 SPIN Cohort participants completed assessments, of whom 986 completed the SEMCD Scale; of these, 524 (53%) met SPIN-SELF eligibility criteria. Over 50% of SPIN-CHAT [27] participants were recruited externally, and we expect similar external recruitment for SPIN-SELF to supplement SPIN Cohort participants, which will allow us to meet our recruitment target.

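### The primary model has no term for peer facilitator; if facilitators lead more than one group and differ in effect, the standard error of the treatment effect is too small

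*Protocol article*

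**What the plan says.** The Data analysis section sets one random-effects structure for every outcome: "For all models, to account for clustering in the blocked PN-RCT design", the model has a random intercept and treatment slope for each randomization block, plus a random treatment slope for each intervention group. Facilitator does not appear. The cluster bootstrap for the complier analysis resamples blocks and participants, again without facilitators.

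Under Random selection and allocation, each pool supplies one block of 12 to 20 people, and half of them form a single intervention group of 6 to 10.

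Under Intervention and comparator: "Each videoconference-based intervention group will be led by a person with SSc who previously received training as a support group leader". On preparation: "prior to the trial, each peer facilitator will receive 4 additional training hours divided into 3 sessions". The article gives no number of facilitators, no caseload and no rule for assigning them to groups.

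The Sample size section uses one intra-class correlation of 0.08, "a mean of 8 participants per group", and an "assumed effect size of SMD = 0.30", arriving at 471 evaluable and 524 enrolled participants.

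**The concern.** The facilitator moderates discussion, supports goal setting and encourages motivation. The primary outcome is self-efficacy, so some of the variation between groups may come from who leads them. If one person leads several groups, those groups share that person's effect and are not independent. A group-level random effect handles correlation within a group but not correlation between groups. Because block and group coincide in the treated arm, the model spends two treatment slopes on one level and has none for the level above.

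Several features make repeat use plausible. About 33 groups are needed, new ones start roughly monthly, and leaders must themselves have a rare disease, hold earlier support-group training and receive further training before the trial. At stake is the width of the primary confidence interval and the true level of the primary test.

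**Working it through.** **Inputs from the protocol.** SMD 0.30; two-sided 5% ("All analyses will be 2-sided with *α* = 0.05"); equal allocation ("With a 1:1 randomization ratio"); group size m = 8; ICC 0.08; 471 evaluable, 524 enrolled.

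**Inputs not in the protocol (assumptions).** k = groups per facilitator; f = share of between-group variance due to the facilitator. Facilitators are taken to have equal caseloads, and a normal approximation is used.

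**Step 1: reproduce the planned size.** Take residual variance 1 and between-group variance θ = 0.08/0.92 = 0.0870 in the treated arm.
- c = (1.960 + 0.842)²/0.30² = 87.21
- N = 2c(2 + mθ) = 2 × 87.21 × 2.6957 = 470.2, so 471 (power 80.1%)
- 471/0.9 = 523.3, so 524

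Both figures match. They imply 471/2/8 = 29.4 evaluable groups, or 524/2/8 = 32.75 groups as enrolled, all treated as independent.

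**Step 2: split the between-group variance.** With n = 235.5 per arm and G = 29.44 groups:
- True variance: V = 2/n + θ(1 − f + fk)/G
- Variance the group-only model is expected to report: M = 2/n + θ[1 − f + f(G − k)/(G − 1)]/G. The last term is slightly reduced because groups sharing a facilitator scatter less around their mean.
- Actual type I error: 2[1 − Φ(1.96 √(M/V))]

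**Step 3: one case in full (k = 3, f = 0.5).**
- V = 0.008493 + 0.0870 × 2/29.44 = 0.01440; SE 0.1200
- M = 0.008493 + 0.0870 × 0.9648/29.44 = 0.01134; SE 0.1065
- Ratio 0.888; error 8.2%

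**Step 4: range.**

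| k | f | True SE | Model SE | SE too small by | Type I error |
|---|---|---|---|---|---|
| 1 | any | 0.1070 | 0.1070 | 0% | 5.0% |
| any | 0 | 0.1070 | 0.1070 | 0% | 5.0% |
| 2 | 0.10 | 0.1084 | 0.1069 | 1.3% | 5.3% |
| 2 | 0.25 | 0.1104 | 0.1069 | 3.2% | 5.8% |
| 3 | 0.50 | 0.1200 | 0.1065 | 11.2% | 8.2% |
| 4 | 0.75 | 0.1345 | 0.1059 | 21.3% | 12.3% |

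**Step 5: check on scaling.** Setting total variance to 1 in the treated arm, with 262 per arm and 32.75 groups, gives 5.3%, 5.7%, 8.1% and 12.0% for the last four rows. That scaling does not reproduce the planned N (it gives 447), but the error rates barely change. A simulation of block-level differences (40,000 trials per case, t reference) gave 5.7%, 7.8% and 11.6% for the last three rows.

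**The case against.** The strongest objection is that the premise is not in the document. No section says that any facilitator leads two groups, and the text is compatible with one leader per group. A condensed article may leave staffing to the full protocol. Nor does anything split the ICC: group composition, schedule, language and calendar time also vary by group. Common training, a fixed session outline, shared online modules and checklist review of 25% of recorded sessions should all limit differences between facilitators. The 471 and 524 are arithmetically right, and group-level clustering is both modelled and budgeted for.

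All of that stands, and it rules out two stronger readings that a reader might infer. One is that the planned standard error is wrong as it stands; this needs both k > 1 and f > 0, and the article establishes neither. The other is that clustering is ignored; only a possible level above the group is absent.

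The objection does not remove the point, because the model is stated, and stated for all outcomes, without a term that would cope if facilitators repeat. Treating facilitators as fixed would make the group-level standard error adequate only for inference about those individuals. Under Ethics and dissemination, the protocol plans later delivery by trained peer facilitators through patient organizations, which points to a wider target.

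**Conclusion.** The point holds conditionally. The specified model treats about 33 intervention groups as independent and carries a redundant treatment slope where a facilitator slope could sit. If some facilitators lead several groups and differ in effect, the standard error is understated and the primary test is liberal. The illustrative type I error runs from 5.3% (2 groups each, 10% share) through about 8% (3 groups, 50%) to about 12% (4 groups, 75%). With one group per facilitator or no facilitator variance, there is no error at all. The caseload and the share are assumptions; the ICC, group size and sample size are the protocol's own. The direction is certain under those conditions, but the size cannot be fixed from the document.

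**What to change.** State the number of facilitators and the groups each will lead, and record the facilitator of each group. Before outcome data are seen, replace the intervention-group treatment slope with a random treatment slope by facilitator, (0 + arm | facilitator). Keep the block intercept and block slope, which continue to carry group-level variance. If every facilitator leads one group, facilitator, group and block coincide and this is the planned model.

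Use Satterthwaite or Kenward-Roger degrees of freedom. With few facilitators the extra term alone is not enough: in a balanced simulation with 8 facilitators, 4 groups each and a 75% share, a 1.96 cut-off still left about 7.5% error. If facilitators repeat, the complier bootstrap should also resample at facilitator level.

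The cost is one data field that the team will already know and one model term. The price is a wider interval if facilitators differ, and fewer degrees of freedom if they are few.

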### SPIN Cohort participants

To be eligible for the SPIN Cohort, participants must meet 2013 American College of Rheumatology / European League Against Rheumatism SSc classification criteria [37]; be ≥18 years old; be fluent in English, French, or Spanish; and be able to respond to questionnaires via the internet. The SPIN Cohort is a convenience sample. Eligible SPIN Cohort participants are recruited and provide written consent at one of one of 47 SPIN sites [18] from Canada, the USA, the UK, France, Spain, Mexico, and Australia during regular medical visits. Site personnel submit an online medical data form to enroll participants, after which participants receive an automated email with instructions to activate their account and complete online SPIN Cohort measures. Cohort participants complete outcome measures via the Internet upon enrollment and subsequently every 3 months. Participants consent to allow their data to be used for observational studies and be contacted by SPIN personnel about other SPIN studies. To date, over 2000 people have enrolled (1615 active) [18].

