### SPIN-SELF trial participants

We plan to enroll 40 English-speaking participants in the feasibility portion of the trial and a total of 524 English- and French-speaking participants in the full-scale trial (including feasibility participants if progression occurs). Eligible participants must (1) meet 2013 American College of Rheumatology / European League Against Rheumatism SSc classification criteria [37], verified via SPIN Cohort enrollment or self-report by external trial participants that they were classified as having SSc by a rheumatologist or internist; (2) have low to moderate disease management self-efficacy (Self-Efficacy for Managing Chronic Disease (SEMCD) Scale [38] ≤ 7.0); and (3) not have been enrolled and assigned to the intervention arm of the initial SPIN-SELF Feasibility Trial [20] (control participants were not notified about the trial and had outcomes assessed via regular cohort assessments). Due to the smaller number of French-speaking participants in the SPIN Cohort, only English-speaking participants will be included in the feasibility portion of the trial to ensure there will be an adequate number of French-speaking participants in the full-scale RCT.

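### The imputation variable list names neither linkable post-randomisation cohort SEMCD scores nor recruitment source

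*Protocol article*

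**What the plan says.** All of this comes from the protocol article.

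- **Cohort schedule** (SPIN Cohort participants): "Cohort participants complete outcome measures via the Internet upon enrollment and subsequently every 3 months". The same section puts the active cohort at 1615 people.
- **The SEMCD is a cohort measure** (Sample size): between March and June 2021, "1007 SPIN Cohort participants completed assessments, of whom 986 completed the SEMCD Scale".
- **Source of trial data** (Data collection and management): "Baseline measures will be completed through regular SPIN Cohort assessments for SPIN participants and through *Qualtrics* for externally recruited participants". The 3- and 6-month outcomes come from Qualtrics for everyone.
- **Linkage** (same section): cohort enrollees keep their SPIN Cohort identification numbers, and an email check ties their trial entry to their cohort record.
- **Imputation** (Data analysis): chained equations with 20 datasets and 15 cycles. The named variables are randomisation block, arm, number of sessions attended, "measures of all primary and secondary outcomes at baseline and at 3 and 6 months post-randomization", age, sex, disease subtype, years since diagnosis, country and race/ethnicity. The stated purpose is to keep bias from missing outcomes small. Complete-data results will also be shown.

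No cohort score after baseline is named as an imputation variable, and neither is whether a participant came from the cohort or from outside it.

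**The concern.** Take a control participant who answers neither follow-up survey. The listed model then predicts the primary outcome from baseline scores, demographic and disease characteristics, block and arm. An intervention participant adds the number of sessions attended. Neither has any post-randomisation measure of self-efficacy. If that person is a cohort member and still answers the cohort questionnaire, such a measure exists, on the same instrument and under an identifier that the trial already holds. Using it would make the missing-at-random assumption more credible where it is weakest, and would recover a little precision.

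Recruitment source is a separate and simpler omission. Cohort and external participants differ in how the diagnosis is verified, in the baseline platform and in the recruitment route, so their drop-out may differ too. The variable is known for all participants.

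**Working it through.** **1. The plan's own sample size.** Inputs from Sample size: SMD 0.30, two-sided α 0.05, 80% power, 8 per group, ICC 0.08. Clustering is in the intervention arm only, with residual variance 1 in both arms.
- Between-group variance = 0.08 / (1 − 0.08) = 0.087.
- Intervention-arm variance factor = 1 + 8 × 0.087 = 1.696.
- Total N = 2 × (1 + 1.696) × (1.960 + 0.842)² / 0.30² = 470.2, rounded up to 471, which is the stated figure.
- Power at 471 = Φ(0.30 / √(2.696 / 235.5) − 1.960) = 80.1%.
- With 10% loss, 471 / 0.90 = 523.3, rounded up to 524, as stated.

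**2. Participants concerned.** Expected losses are 524 − 471 = 53. The cohort share of these is not given. The article expects external recruitment similar to an earlier trial in which it exceeded 50%, so I assume half: 26.5 people.

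**3. How many would have a cohort score.** By the article's counts, 986 / 1615 = 61% of active members gave a SEMCD in one 3-month window. The yield among trial non-responders is unknown. Taking 61% to 100% gives 26.5 × 0.61 = 16 to 26.5, or about 27. With a cohort share of 25% to 75%, the range is 8 to 40.

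**4. Effect on bias.** Suppose missing scores in one arm lie 0.5 SD from what the listed variables predict (an assumption). The bias is 0.10 × 0.5 = 0.05 SD, one sixth of 0.30. If drop-out depends on the outcome itself, an auxiliary with partial correlation ρ removes a share ρ² for each person who has it: 0.36 at ρ = 0.6 and 0.49 at ρ = 0.7 (both assumed).
- Lower end: 0.05 × 0.5 × 0.61 × 0.36 = 0.0055 SD.
- Upper end: 0.05 × 0.5 × 1.00 × 0.49 = 0.012 SD.

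The bias would thus fall from 0.05 to about 0.038–0.044 SD. The part removed is about 2% to 4% of the target effect. If the cohort score were shifted by as many SDs as the missing outcome, the share removed would be ρ instead of ρ², and the range 0.05 × 0.5 × 0.61 × 0.6 = 0.009 to 0.05 × 0.5 × 0.7 = 0.018 SD. That is still small.

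**5. Effect on power.** Approximate gain in effective N = people with a score × ρ².

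| Assumed ρ | Gain in effective N | Power (80.1% at 471) |
|---|---|---|
| 0.6 to 0.7 | 16.2 × 0.36 = 5.8 to 26.5 × 0.49 = 13.0 | 80.5% to 81.1% |
| 0.5 to 0.9 | 16.2 × 0.25 = 4.0 to 26.5 × 0.81 = 21.5 | 80.4% to 81.8% |

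**6. Timing.** On a 3-month (13-week) cycle, the nearest scheduled assessment lies within about 13 / 2 = 6.5 weeks of any trial time point. A score 6 weeks before month 3 falls at about week 7. Table 2 places sessions 6, 7 and 8 at weeks 8, 10 and 12, so such a score would come before three of the eight sessions.

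**The case against.** The strongest reply is that nothing stated in the article is wrong. The list is introduced in open wording, the article is condensed, and an unseen SAP may add auxiliary variables. The list is also richer than a bare set of baseline variables: sessions attended bears directly on people who stop the programme, and each follow-up time point informs the other. This stands, and it makes the point one of robustness and not of error. It does not dispose of the point. The list is itemised in detail, and the article says that the analysis cannot be blinded, so auxiliaries are better named in advance than chosen with the data in view.

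The second reply is that the size is small. Loss in the two earlier group-format trials was well below 10%, and half is near the upper end of the cohort share that the article expects. This stands too.

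The third reply is that the cohort score does not exist for external participants. This is true. It complicates the imputation model but does not rule the score out.

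A reader might infer more than the documents support:

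- **That cohort members who leave the trial surveys keep giving a SEMCD every 3 months.** The article gives a schedule and, by its own counts, a 61% yield among active members. Non-response to two online surveys from the same network is probably related. The article also does not say whether cohort assessments run unchanged during the trial.
- **That a cohort score could stand in for a missing trial outcome.** The earlier SPIN-SELF trial may seem a precedent, since its "control participants were not notified about the trial and had outcomes assessed via regular cohort assessments". That was a different design, which this trial has given up. Here outcomes are anchored to randomisation and collected in one way from everyone, and step 6 shows that a substituted score could be a mid-programme value.
- **That the consent fails to cover this use.** The consent form is an additional file that is not shown, so no finding can rest on it.

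**Conclusion.** The point holds as a modest weakness. A scheduled, linkable series of the primary measure exists for cohort members. The stated imputation list names none of its post-randomisation scores, and it leaves out recruitment source for everyone. No figure in the plan is wrong, and the sample size reproduces.

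Under the assumptions above (10% loss, half cohort share, 61% to 100% yield, 0.5 SD shift in one arm, partial correlation 0.6 to 0.7), the bias removed is about 0.006 to 0.012 SD out of 0.05 SD. Power gains at most 1 to 2 points. The one-sixth figure in step 4 describes the assumed bias and not what the change would recover. The case rests on a more credible missing-at-random assumption for some of those lost, obtained at low cost. The cohort share, yield, shift and correlations are not in the documents.

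**What to change.** Add to the imputation paragraph in Data analysis, or to the SAP:

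1. For cohort members, the post-randomisation cohort SEMCD scores nearest to months 3 and 6, each with its days from randomisation, enter the mice model as auxiliary variables.
2. Recruitment source (cohort or external) enters for all participants.
3. Cohort scores are not substituted for the 3- or 6-month trial outcome.
4. The treatment of the cohort score in external participants, where it does not exist, is stated: for example, imputation within recruitment source, or a model in which the score acts only for cohort members.

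Cohort members who answer both surveys show how closely the two scores agree, so the weight given to the cohort score can be estimated from the data. It would help to report how many participants with a missing trial outcome had a cohort score.

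The cost is a few sentences, a data extraction through identifiers already in place, and a slightly more complex imputation model. The auxiliary helps cohort members only, and its timing is inexact. The sample size does not change.

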### Random selection and allocation

For the feasibility and full-scale portions of the trial, consented participants will be entered into pools of participants available to participate in the same weekly group based on availability and, for the full-scale trial, language. For the full-scale trial, separate English- and French-language groups will be formed (feasibility only includes English-speaking participants). De-identified codes for participants in each pool will be provided to an external randomization service. Starting with the largest pool, the service will randomly select the largest possible even number of participants (12 to 20 participants to obtain intervention groups of 6 to10 participants) then randomly allocate half to intervention and half to control via single block randomization using R version 3.6.3. For the feasibility trial, depending on scheduling availability and pool sizes, we will form 2–3 pools. For the full-scale trial, we will form as many pools as possible each month until the enrollment target is met.

All participants who are randomized will receive an email to communicate their assignment to the SPIN-SELF Program or usual care. The intervention group email will include the date and time of their first group session and information on how to access SPIN-SELF Program and login to the videoconferencing system. Participants who have not been randomly assigned to either the intervention group or the waitlist will receive an email to inform them that they could not be assigned but will be re-contacted to confirm eligibility and interest and attempted to be randomized when new sessions begin again in a month.

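### If the complier-effect bootstrap redraws participants inside redrawn blocks, as its wording suggests, its 95% CI is roughly 20–30% too wide; the primary analysis is unaffected

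*Protocol article*

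**What the plan says.** The Data analysis section estimates the effect among compliers with an instrumental variable approach, to "inflate intent-to-treat effects from main models by the inverse probability of compliance among intervention arm participants". For the interval it says that "95% CIs will be constructed via a cluster bootstrap approach, resampling at study randomization block and participant levels". Two levels are named as resampled. The text does not say that participants of a drawn block stay together, and it gives no correction for a second stage. It cites two sources for the method.

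The block structure is in the Random selection and allocation section. Each pool yields a block of "12 to 20 participants to obtain intervention groups of 6 to10 participants", and the service will "then randomly allocate half to intervention and half to control via single block randomization". One block is therefore one intervention group plus an equal number of controls. The Sample size section plans "a mean of 8 participants per group" and an intra-class correlation (ICC) of 0.08.

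The main models from which the intent-to-treat effect is taken include a fixed effect for baseline score.

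**The concern.** A cluster bootstrap imitates the sampling of independent units. Here these are the blocks. Each observed block difference already carries the error of its own participants, so drawing blocks with replacement reproduces the between-block and the within-block parts of the variance together. Drawing participants again with replacement inside each drawn block adds the within-block part a second time. With about 8 per arm and a low ICC, the within-block part is most of the total, so the excess is not trivial.

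At stake is consistency between two reported results. The complier estimate is the intent-to-treat effect divided by a compliance proportion, so its interval should exclude zero in nearly the same cases as the intent-to-treat interval. With an interval 1.30 times too wide, an intent-to-treat result at z = 1.96 would sit beside a complier result at about z = 1.96/1.30 = 1.5. The article could then show an intent-to-treat effect next to an apparently inconclusive complier effect, purely because of the resampling scheme.

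**Working it through.** **Inputs from the protocol article.** Mean group size m = 8, range 6 to 10; ICC 0.08, intervention arm only; 1:1 allocation within block; SMD 0.30; analysed N = 471 and randomized N = 524. Number of blocks: 471/16 ≈ 29 analysed, 524/16 ≈ 33 randomized. Assumed, because the article gives no figure: compliance 0.7 (varied from 0.5 to 0.9), baseline–outcome correlation r of 0.4 to 0.7, and the between-block variances noted below.

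**The plan's own figure first.** The article gives no figure for the bootstrap interval, but its sample size checks the inputs. With residual SD 1 in both arms:
- n per arm = (1.960 + 0.842)²/0.30² × [(1/0.92)(1 + 7 × 0.08) + 1] = 87.2 × 2.696 ≈ 235.1
- N = 470.2, rounded up to 471; 471/0.9 = 523.3, rounded up to 524. Both stated figures are reproduced.

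**Variance of one block's arm difference** (total variance 1 in each arm):
- Within-block part: W = (0.92 + 1)/8 = 0.24
- Total: V = 0.08 + 0.24 = 0.32

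**What each scheme estimates** with k = 29 blocks:
- Block-only: V(k−1)/k = 0.32 × 28/29 = 0.309
- Added by redrawing participants: W(m−1)/m = 0.24 × 7/8 = 0.21
- Two-level: 0.309 + 0.21 = 0.519

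**Width ratios without baseline adjustment:**
- Against block-only: √(0.519/0.309) = 1.30
- Against the true sampling SD: √(0.519/0.32) = 1.27

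Under the scaling that reproduced N = 471 (residual SD 1, group variance 0.08/0.92 = 0.087, W = 0.25) the first ratio is 1.29, so the scaling hardly matters.

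**With baseline adjustment.** The within-block part shrinks by 1 − r² and the group variance is taken as unchanged:

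| r (assumed) | W | V | vs block-only | vs true SD |
|---|---|---|---|---|
| 0 | 0.240 | 0.320 | 1.30 | 1.27 |
| 0.4 | 0.202 | 0.282 | 1.28 | 1.26 |
| 0.7 | 0.122 | 0.202 | 1.24 | 1.22 |

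**Other sensitivities, against block-only, unadjusted:**
- Group size 6, 8, 10: 1.30, 1.30, 1.29
- ICC 0, 0.05, 0.10, 0.20: 1.38, 1.32, 1.28, 1.22
- Treatment heterogeneity between blocks of variance 0.05 (assumed): 1.26
- Compliance 0.5, 0.7, 0.9, by simulation: 1.30 to 1.31

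**Simulation of the ratio estimator.** 29 blocks of 8 + 8, ICC 0.08, compliance 0.7, block variance 0.05 (assumed), generalized least squares with random block intercept and slope, no baseline covariate, percentile intervals, 2000 trials:

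| Scheme | Width vs block-only | Width vs true SD | Coverage |
|---|---|---|---|
| Blocks only | 1.00 | 0.96 | 93.1% |
| Two-level, participants drawn within arm | 1.31 | 1.26 | 98.3% |
| Two-level, not stratified by arm | 1.32 | 1.27 | 98.4% |

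With 33 blocks (1000 trials) coverage was 92.6%, 97.9% and 98.2%. A normal approximation at the adjusted ratio of 1.22 also gives about 98%, since 1.96 × 1.22 = 2.39.

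**Practical size.** Unadjusted simulation: true SD 0.151, block-only SE 0.147, two-level SE 0.192; complier effect 0.30/0.7 = 0.429. The chance that the interval excludes zero is Φ((0.429 − 1.96 × 0.192)/0.151) ≈ 64% for two-level and Φ((0.429 − 1.96 × 0.147)/0.151) ≈ 82% for block-only. Baseline adjustment would narrow this gap.

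**The case against.** **The wording does not fix the algorithm.** The sentence never says that participants are drawn with replacement inside drawn blocks, and it defers to two cited sources. Two procedures avoid the double count: drawing blocks with replacement and participants without, which leaves each block whole; or resampling block-level and participant-level residuals from the mixed model. This stands as a limit. The size above is conditional on with-replacement sampling at the second stage. It does not remove the point, because naming the participant as a resampled level most naturally means that participants are redrawn.

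**A flat 30% ignores the planned model.** This stands. The complier effect is built from models that adjust for baseline score, and adjustment shrinks exactly the part that is counted twice. Hence the range of roughly 20–30%.

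**The harm is limited.** This also stands. The interval errs on the wide side. The intent-to-treat intervals come from the mixed model with Rubin's rules, and no decision in the article hangs on the complier interval. A reader might infer that the trial's main conclusion is compromised, or that a clear effect would routinely be lost. The document supports neither: the primary analysis does not use this bootstrap, and only fairly borderline complier results would change sides.

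**Block-only resampling is not exact either.** Correct. It covers about 92–94% with about 30 blocks, so the remedy needs a small-sample adjustment. It is still nearer to 95% than the two-level scheme.

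**Conclusion.** The point holds in a bounded form. As worded, the scheme most naturally redraws participants inside redrawn blocks. At the article's ICC and group size the complier interval is then roughly 20–30% too wide: about 30% without baseline adjustment and about 20–28% with an assumed baseline correlation of 0.4–0.7. Coverage is about 98% instead of 95%.

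This rests on with-replacement sampling at both stages and on the planned ICC of 0.08. The assumed compliance hardly matters. If participants are in fact kept whole within drawn blocks, there is no excess and only the wording needs correcting. The error is conservative and confined to the complier analysis; the primary intent-to-treat result and the sample size of 471 (524 randomized) are untouched. It is worth correcting because the correction is nearly free.

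**What to change.** Replace the two-level phrase with a statement that whole randomization blocks are resampled with replacement and all participants of each drawn block are kept. State also that both the intent-to-treat effect and the compliance proportion are recomputed in each replicate.

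Add a small-sample adjustment for about 30 blocks, for example a k/(k−1) variance factor or a bootstrap-t interval. With k = 29 the factor widens the interval by √(29/28) = 1.018. By arithmetic that takes the simulated block-only width from 0.96 to about 0.98 of the ideal, so it closes only about half of the gap.

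If the authors intended a residual bootstrap or intact blocks, saying so resolves the matter equally well. The cost is one or two sentences. Resampling blocks only needs no more computing than the two-level scheme; a bootstrap-t interval would need somewhat more.
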